#### Health-related quality of life by EuroQol 5 dimensions health state questionnaire (EQ-5D) and quality adjusted-life years (QALY)

EQ-5D [50, 51] is a generic measure of health status consisting of five dimensions (mobility, self-care, usual activities, pain/discomfort, anxiety/depression), each with responses indicating three levels of severity (no problems, some or moderate problems, extreme problems). The EQ visual Analogue scale (EQ-VAS) is a standard vertical 20 cm VAS recording people’s rating of their current health-related quality of life (HRQoL) ranging from ‘the best health you can imagine’ to ‘the worst health you can imagine’ [50, 51]. The EQ-5D index will be used to derive QALY using the Swedish experience-based value set [52] and an area-under-the-curve calculation [53]. An alternative valuation using a general population value set from the UK [54] will be part of the sensitivity analysis, as Sweden has no such societal valuation.

#### ICEpop CAPability measure for older people (ICECAP-O) and capability-adjusted life years (CALY)

The ICECAP-O capability index [55, 56] estimates quality of life (QoL) in a broader sense compared to the HRQoL, including five attributes (attachment, role, enjoyment, security, control), each with four response levels. The ICECAP-O instrument will be used to derive CALY using the British valuation [56].

#### Change in daily activities based on the Activities of Daily Life (ADL) staircase

Change in dependence in daily activities will be assessed based on the ADL staircase [57, 58]. The Instrument contains a cumulative scale of six personal activities (P-ADLs: bathing, dressing, going to the toilet, transfer, continence, feeding) and four instrumental activities (I-ADLs: cleaning, shopping, transportation, cooking). Dependence is defined as receiving personal or directive assistance from another person [57, 58]. In line with previous studies [59, 60] evaluating ADL in frail older people, a participant living with another person is assessed as “independent” if they are capable of performing the activity without assistance when alone.

#### Societal costs

Resource use in the economic evaluation will include register data on health care use (held by the Region Västra Götaland), as well as dispensed drugs, and use of social care use (held by the National Board of Health and Welfare). Informal care and other expenses to the participant and family and friends related to the treatment will be collected using patient questionnaires and based on user data from the digital platform. Costs (both reimbursements and out-of-pocket costs) for prescribed drugs will be obtained from the Swedish Prescribed Drug Register (SPDR) [46]. The out-of-pocket costs for healthcare use and social care will be calculated from national statistics on patient fees while accounting for the national high-cost protection schemes, in line with previous work [61]. Regional costs for healthcare will be calculated using cost-per-patient data and diagnosis-related group weights (DRG) from specialised care and the national mean cost for producing one DRG, while the corresponding costs for primary care and social care will be derived using national cost statistics. Additional questions have been added in the questionnaire to identify expenses not accounted for in register data. Informal care costs will be viewed as a direct cost, and thus valued at the average wage and social security contribution of employing a formal caregiver, sometimes called the replacement cost approach [62].

#### Incremental cost-effectiveness ratio (ICER)

The ICER will be calculated as the societal cost difference between groups divided by the corresponding difference in QALY [52] and CALY [56], respectively as recommended in studies including both health and social services [63, 64].

#### Change in the burden of medicine use in everyday life based on The Living with Medicines Questionnaire version 3 (LMQ-3)

Participants will self-rate eight domains: relationship with health professionals, practical difficulties, interference with daily life, lack of effectiveness, side effects, general concerns, cost, and lack of autonomy. Each domain will be rated on a 5-point Likert scale (strongly agree to strongly disagree) [65].

#### Change in the participants’ self-rated overall level of burden of medicine

Participants will assess the overall level of burden of medicine on a 10 cm VAS from 0 (no burden at all) to 10 (extremely burdensome) [65].

#### Social network, social support, and loneliness

Five items will ask about social network, sufficient support, someone to trust and confide in, experience safety and security and feelings of loneliness [66–68].

#### Self-reported frailty indicators according to the Tilburg Frailty Indicator (TFI)

The TFI [67, 68] will be used to assess self-reported frailty indicators, unexplained weight loss, difficulty in walking, strength in hands, physical health, physical tiredness, balance, problem with hearing and vision (physical domain), cognition, depressive symptoms, anxiety, and coping (psychological domain), living alone, social relations and social support (social domain). An additional question about falls during the past 3 months will also be used [66].

#### Frailty according to the clinical Frailty Scale (CFS) version 1.2

The degree of frailty will be assessed from 1 to 9; 1: very fit, 2: well, 3: manging well, 4: vulnerable, 5: mildly frail, 6: moderately frail, 7: severely frail, 8: very severely frail, 9: terminally ill) [69].

For details about primary and secondary outcomes, data sources, and time points for data collection, see Table 1.

**Table 1 Tab1:** Overview of primary and secondary outcomes, demographic measures, data sources, and time points for data collection

	Research assessment/data source/register data	T0 baseline	T1 3 months	T2 6 months	T3 12 months	Retrospectively collected
Primary outcomes						
A composite of clinical changes in general self-efficacy and the need for hospital care for unscheduled reasons at 3 months	Questionnaires	x	x			
	Medical records from baseline up to 3 months and register data					
**Secondary outcomes**						
A composite of changes in general self-efficacy and the need for hospital care for unscheduled reasons at 6 and 12 months	Questionnaires	x		x	x	
	Medical records from baseline up to 12 months and register data					
Health-related quality of life	Questionnaires	x	x	x	x	
Capability-related quality of life according to ICECAP-O	Questionnaires	x	x	x	x	
Hospitalisation	Questionnaires, Medical records					x
General self-efficacy	Questionnaires	x	x	x	x	
Change in ability to perform activities of daily living according to the ADL staircase	Questionnaires	x	x	x	x	
Societal costs	Register data, Questionnaires, Digital platform data, and Communication lists.					x
Incremental cost-effectiveness ratio	Questionnaires Registers	x	x	x	x	x
Change in the burden of medicine use in everyday life according LMQ-3	Questionnaires	x	x	x	x	
Change in the participants’ self-rated overall level of burden of medicine	Questionnaires	x	x	x	x	
Social network, social support, and loneliness five questions	Questionnaires	x	x	x	x	
**Demographics**		x				
Background questions, six questions	Questionnaires	x				
Self-reported frailty according to the TFI	Questionnaires	x				
Frailty according to CFS	Researchers’ objective assessment	x				

ICEpop CAPability measure for Older people (ICECAP-O), Activities of Daily Life (ADL), Living with Medicines Questionnaire version 3 (LMQ-3), Tilburg Frailty Indicator (TFI), Clinical Frailty Scale (CFS).

### Blinding

The nature of the intervention means that neither participants nor the HCPs in the IHOPe intervention can be blinded to allocation in the RCT.

### Sample size and power calculation

In the full-scale RCT and health economic evaluation a minimum of 220 patients must be randomised to the two arms based on the primary outcome measure. To achieve 80% power based on a p-value of 0.05 and allow an increase in the proportion of improved or unchanged patients from 20 to 40%, 91 participants in each group (control and intervention) are required. We plan to include 110 patients in each group to have a comfortable margin for dropouts and withdrawals.

### Timeline

Recruitment of participants started in the spring of 2020 and is expected to be completed in 2023. The intervention will continue until early 2024. Data for the primary outcome will be collected three months after the last patient inclusion. Data collection for the secondary outcome measures will continue until early 2025. After that, retrospective register data will be obtained as there is a delay from data collection to transmission to the administrative registers.

### Data analysis

Analysis will be performed according to two analysis sets: (1) the intention to treat set, meaning that all allocated participants will be analysed in the group to which they were randomised [70] and (2) the per-protocol set, which includes only those participants who at least have one telephone conversation and an agreed health plan to indicate an expected minimum level of participation.

If necessary, eventual differences between the intervention and control group at baseline will be adjusted for in the analysis. Different options for handling missing data will be considered based on the collected data. Missing data due to death will be replaced with a value for worst-case change (deteriorated in the composite of primary outcomes). Based on the assumptions that the study sample is expected to decline over time due to the ageing process and that deteriorated health is a common reason not to fulfil follow-ups, the imputation model of median change deterioration will likely be used. However, the final decision on how to handle missing data will be decided by the research team in consultation with a statistician.

Descriptive and analytical statistics will be used to compare the control and intervention groups and to measure change over time. The chi-square or Fisher’s exact test will be computed to compare the proportions between groups. Logistic regression will be used to calculate odds ratios (ORs) with 95% confidence intervals (CIs). Parametric tests will be performed when suitable, and non-parametric tests will be applied when analysing ordinal data.

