**Fig. 1 Fig1:**
[figure not shown]
Flow chart of participant enrolment, allocation, follow-up, and analysis [35]

Participants aged ≥ 75 years will be screened using an instrument developed by the Frail Elderly Support Research Group (FRESH) [39] as part of usual care at the emergency department or by a research assistant via telephone. The screening results (if frail or not) will be documented. The research assistant will screen patients identified as frail for eligibility to participate in the study using the above-mentioned inclusion and exclusion criteria and the electronic patient record. A study information letter and invitation to participate will be sent to eligible patients within two weeks after their emergency visit. The patient will then be contacted by telephone to provide verbal information and asked about consent to participate. Finally, written participant information and informed consent forms will be sent to patients willing to participate.

All who fulfil the inclusion criteria and consent to participate will be randomised into the study. Participants will be randomly assigned to the control or the intervention group with a 1:1 allocation using a computer-generated randomisation schedule. The control group will receive usual care whilst the intervention group will receive the person-centred e-support intervention for six months in addition to usual care.

The recruitment of participants to the main study started after the inclusion of 17 participants in a pilot study. The full-scale RCT is currently ongoing. Follow-up for each study participant continues for 12 months from inclusion.

Recruitment of significant others and HCPs depart from the older people’s network by contact information to significant others or formal carers invited to the intervention.

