### Control group

The participants allocated to the control group will receive *usual care*. Routine care for older people in Sweden includes care delivered by diverse HCPs in hospital, primary care, municipal, and home care services. Also, informal carers are often involved. It is unusual to have any follow-up contact from the emergency ward for frail older people who are not admitted to hospital. However, within usual care some patients are contacted by a ‘mobile team’ (consisting of nurses and physicians) through a coordinator at the emergency ward. The mobile team visits the patient at home or contacts the municipal care provider for further follow-up, depending on the older person’s healthcare needs and status [40]. However, the mobile team does not deliver digital healthcare.

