### Intervention group

In addition to usual care, participants allocated to the intervention group will receive person-centered telephone support and the opportunity to communicate with HCPs through the digital platform for six months. The intervention is delivered remotely and is coordinated by dedicated registered nurses (RNs). The HCPs conducting the intervention receive continuous training through workshops with specialists in PCC, ethics, communication, and pedagogics on how to apply remote PCC.

Intervention components.

The intervention aims to initiate partnership-building, encourage older people to describe their health situation and needs, and further identify and engage their capabilities and resources [43].

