### Telephone support and the creation of a health plan

An HCP will initiate the first telephone conversation shortly after study inclusion (within two weeks). After the first telephone call, a follow-up appointment will be mutually planned and agreed upon between the HCP and the older person. In addition, there is the opportunity for incidental contact with the older person by telephone or through the digital platform. The participants’ narrative of their everyday situation, as well as their needs, resources, and health-related goals are the core components of the telephone conversations [11, 41]. The conversation will start with recapitulating the aim of PCC support, asking open-ended questions, and listening to the participants’ experience of their condition, context, needs, and resources. The HCP will confirm and summarise the content of the conversation and, in collaboration with the participant, co-create achievable and relevant health-related goals. The participants’ narratives (at times in partnership with significant others), goals, and strategies to manage everyday life, as well as needs of support and actions and resources to achieve agreed health-related goals, will then be documented in a health plan by either the participant or the HCP and uploaded to the digital platform. This health plan is, however, a living document and can be modified and reformulated during the intervention, as is described in other PCC projects with different populations [22, 42, 43].

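### The per-protocol set is defined by intervention components, so it holds no controls if read literally, and if applied to one arm it compares post-randomisation engagers with all controls

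*Protocol article*

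**What the plan says.** The Data analysis section names two sets. One is "the intention to treat set, meaning that all allocated participants will be analysed in the group to which they were randomised". The other is "the per-protocol set, which includes only those participants who at least have one telephone conversation and an agreed health plan", a rule meant "to indicate an expected minimum level of participation". The sentence names no arm and gives no criterion for controls. Neither set is called primary, and the per-protocol set is not called supportive. The same section then says that the statistics will compare the two groups.

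Other sections show who can meet the rule:
- Enrolment and randomisation: "The control group will receive usual care whilst the intervention group will receive the person-centred e-support intervention".
- Intervention group: "participants allocated to the intervention group will receive person-centered telephone support".
- Telephone support and the creation of a health plan: "An HCP will initiate the first telephone conversation shortly after study inclusion (within two weeks"). The narratives, goals and needs that come out of these conversations "will then be documented in a health plan by either the participant or the HCP and uploaded to the digital platform".

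**The concern.** Both conditions for entering the per-protocol set are parts of the treatment under test. Controls are not offered them, so the set as worded cannot yield the between-group comparison that the section announces.

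The workable alternative keeps every control and drops intervention patients who had no call or no agreed plan. Those patients are removed because of something that happened after randomisation, and no matching patients are removed from the control arm. If the people who never get as far as a plan are also those more likely to deteriorate, an ineffective intervention will look beneficial. Because the section does not rank the two sets, a favourable per-protocol result could be read as equal in weight to a null intention-to-treat result. If the reading is chosen only once outcomes are known, that choice also depends on the data.

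**Working it through.** **Step 1: who qualifies.** Both a telephone conversation and an agreed health plan are required. A control may have had a recruitment call or contact from the usual-care mobile team, but nothing in the protocol gives a control an agreed health plan. Literal count: 0 of 110 controls.

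**Step 2: the plan's own figures.** Sample size and power calculation gives 20% versus 40% improved or unchanged, 80% power, p = 0.05, 91 per group required and 110 planned. A two-sided two-proportion formula with continuity correction returns 91, so the figure reproduces. The point here does not depend on it; I take from it only the 20% and 40% rates and the 110 per arm.

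**Step 3: the rule applied to the intervention arm only, with no true effect.** Let p be the success rate (improved or unchanged) in both arms, f the share of the intervention arm without call plus plan, and r the non-engagers' success rate as a fraction of p.

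- Engagers' rate: e = (p − f·r·p) / (1 − f)
- Spurious gain: e − p
- Rejection: exact probability that a two-sided 5% two-proportion z test rejects, with 110 controls against 110(1 − f) engagers (94 at f = 15%, 88 at f = 20%)

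From the protocol: p = 20% or 40%, and 110 per arm. Assumed: f, r and the third base rate, p = 75%. At 75%, r of 67% and 53% correspond to non-engager success rates of 50% and 40%; the same r values are carried to the other base rates.

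| p | f | r | e | Gain (points) | Rejection |
|---|---|---|---|---|---|
| 20% | 15% | 67% | 21.2% | 1.2 | 5.7% |
| 20% | 20% | 53% | 22.3% | 2.3 | 7.0% |
| 40% | 15% | 67% | 42.4% | 2.4 | 6.4% |
| 40% | 20% | 53% | 44.7% | 4.7 | 10.2% |
| 75% | 15% | 67% | 79.4% | 4.4 | 11.5% |
| 75% | 20% | 53% | 83.75% | 8.75 | 32.5% |

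Worked line: p = 40%, f = 20%, r = 53.3% gives non-engagers 21.3% and e = (0.40 − 0.20 × 0.2133) / 0.80 = 0.447.

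**Step 4: how far the range stretches.**
- With f = 5% and the same r, rejection is 5.7-6.3% at p = 75% and 5.1-5.4% at 20% and 40%.
- With r = 1 (non-engagement unrelated to outcome), the gain is zero and rejection is about 5%.
- Taking f from 10% to 30% and r from 0 to 0.75, at p = 20% or 40%, the odds ratio under no effect runs from 1.03 to 2.00 and rejection from about 5% to 64% (normal approximation). The upper end needs 30% non-engagers with no successes among them.

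**Step 5: an estimate that keeps everyone.** In the worked line the whole intervention arm averages 0.80 × 0.4467 + 0.20 × 0.2133 = 0.400. The complier-average estimate is the difference between arms as randomised divided by the share receiving the intervention: (0.400 − 0.400) / 0.80 = 0. The 4.7-point artefact disappears.

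**The case against.** The strongest reply is that nobody intends a per-protocol set without controls. The rule's stated purpose is a minimum level of participation, and the section goes on to compare the groups, so the natural reading is that the rule filters the intervention arm and controls stay. A condensed article may leave the arm-specific detail to the analysis plan. I accept this as to intent: a reader might infer that the trial plans a one-armed per-protocol analysis, and the text does not support that as the aim. The reply does not remove the problem, because the natural reading is the selected comparison of Step 3. Nor is the point one of missing detail: the definition is stated, and as stated it gives an empty or a selected comparison.

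A second reply concerns size and direction. A reader might infer that the per-protocol result is known to be biased towards the intervention, with a false-positive rate of 12-33%. The protocol does not support that. It reports no engagement rate and no outcome for non-engagers, and the 12-33% needs a 75% base rate where its own planning rates are 20% and 40%. Its remark that deteriorated health commonly underlies missed follow-up is about questionnaires, not about taking a call. Patients must be oriented, not hospitalised and reachable by telephone to consent, which screens out some of those too ill to engage. Well patients who see no need for a plan could push the bias the other way. All of this stands, and it limits the claim to a plausible direction and an uncertain size.

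A third reply is that intention to treat is planned, listed first and untouched. That also stands and governs the severity.

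**Conclusion.** The point holds as a defect in a stated rule. Literally, the per-protocol set has no controls; on its workable reading it compares post-randomisation engagers with all controls. On the 15-20% non-engagement and 53-67% relative success assumed here, the distortion under no effect is modest at the protocol's own rates (about 1-2 points at 20%, about 2-5 points at 40%, with rejection of about 6-10% overall). It is larger (about 4-9 points, 12-33%) only at an assumed 75%. It favours the intervention if non-engagers do worse, which is plausible in this population but not shown.

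A reader might also infer that the trial's main conclusion is compromised. It is not: the primary endpoint, the sample size and the intention-to-treat comparison do not depend on this set. Severity is moderate.

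**What to change.** In the Data analysis section, before outcomes are analysed by arm:

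1. Name the intention-to-treat set as primary.
2. State that the call-plus-plan criterion applies to the intervention arm and that all controls are retained.
3. Label the per-protocol analysis supportive, and report the number and baseline characteristics of the patients it excludes.
4. For the effect of actually receiving the intervention, add a complier-average causal effect analysis of all randomised patients. Randomisation is the instrument, receipt is at least one call plus an agreed plan, and receipt is zero for controls.
5. Add a sensitivity analysis that defines receipt as any call.

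Removing the per-protocol set altogether is a matter of preference and is not needed.

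The cost is a few sentences and one further model with a sensitivity run. The complier-average estimate has a wider interval and relies on the exclusion restriction, meaning that allocation affects outcome only through receipt. That assumption is strained for patients who had a call but no agreed plan, since they were partly exposed yet count as untreated, which is why item 5 is included.

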### Primary outcome

In line with previous RCTs evaluating PCC [22, 43] the primary outcome will be a composite of clinical changes [47], in general self-efficacy and the need for hospital care for unscheduled reasons after 3 months. Each participant will be classified as improved, deteriorated, or unchanged at three months as follows:

*Deteriorated*: the participant’s general self-efficacy has decreased by $$\ge$$5 units or has been admitted to hospital for unscheduled reasons two or more times.*Improved*: general self-efficacy has increased by $$\ge$$5 units, and the participant has not been admitted to hospital more than once.*Unchanged*: the patient has neither deteriorated nor improved.

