### Health economic evaluation

Reporting of the economic evaluation will follow the Consolidated Health Economic Evaluation Reporting Standards [71]. Costs will be described and analysed as cost components and total cost, with 95% CIs to indicate uncertainty. Bootstrapping will be used to calculate CIs for any skewed variables [72]. The distribution of costs will also be analysed by major stakeholders: county council/regions, municipalities, market sectors (productivity loss), and individuals/family/friends.

In the case of clearly beneficial effects for costs and intervention outcomes (i.e., lower costs and more health created compared to the alternative) for one of the treatment arms, thus dominating the comparator, this information will be reported. However, increased health benefits are often associated with higher costs, in which case we will use cost-utility analysis to estimate the cost of gaining one additional QALY or CALY, respectively. According to state-of-the-art practice, sensitivity analyses will be applied to test the robustness of the results to necessary assumptions and alternative cost levels. A probabilistic sensitivity analysis will be conducted using longitudinal regression analysis [73] with bootstrapped samples that are visualised using a cost-effectiveness plane. This regression analysis enables adjustment for identified confounding factors. Results from the regression analysis will be compared to the corresponding estimations made using multiple imputations, which have been used more often in previous studies [74].

In addition, group-based trajectory modelling will explore potential cost variations and outcomes within the patient group [75]. This method identifies groups of patients with a similar trajectory in some outcome over time, such as health care costs. The identified groups will then be used to explore patient characteristics associated with such trajectories to provide guidance on which patients would benefit initially from a more intense intervention or are more likely to deteriorate.

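### The rule for missing 3-month outcomes is left to the collected data and favours an undefined single-value fill, which puts most filled cases in one outcome class and can turn unequal dropout into an arm difference

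*Protocol article*

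**What the plan says.** Under Primary outcome, "Each participant will be classified as improved, deteriorated, or unchanged at three months as follows". A participant is deteriorated when "general self-efficacy has decreased by" 5 or more units, or after two or more unscheduled admissions. Improved needs a gain of 5 or more units and also that "the participant has not been admitted to hospital more than once". Everyone else is unchanged. The sample size section powers the trial on the share improved or unchanged, 20% against 40%.

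On missing data, the Data analysis section states: "Different options for handling missing data will be considered based on the collected data". Deaths are set to deteriorated. For the rest, reasoning that the sample will decline with age and that poor health is a common cause of non-response, it says that "the imputation model of median change deterioration will likely be used". The final decision goes to the research team with a statistician. The intention-to-treat set keeps all allocated participants.

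Three other places bear on this. The sample size section says: "We plan to include 110 patients in each group to have a comfortable margin for dropouts and withdrawals". Table 1 gives the admission source for the primary outcome as "Medical records from baseline up to 3 months and register data", alongside the questionnaires. Multiple imputation appears only under Health economic evaluation, where the regression results are to be "compared to the corresponding estimations made using multiple imputations".

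**The concern.** The primary outcome is a score change cut at 5 units. A single filled value cannot spread non-responders over the classes as real changes would; it puts them on one side of the cut. The term used for the fill is not defined, so the document does not say which side.

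If the value reaches -5, the filled cases are failures. If it is -3 or -4, they are unchanged and count as successes, which contradicts the stated reason for the method, namely that non-responders have often got worse. Either way none can be improved, and the chi-square test and logistic regression treat the filled classes as observed, so the uncertainty from missing data is lost.

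Once the filled class is fixed, any difference in dropout between arms passes directly into the primary comparison. Unequal dropout is plausible, because only the intervention arm has continuing professional contact and participants know their allocation. Leaving the choice of rule to the collected data adds avoidable flexibility to the primary analysis.

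**Working it through.** **1. The plan's own figure.** Inputs from the sample size section: 20% against 40%, 80% power, 5% level (taken as two-sided).

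n′ = [1.96·√(2·0.3·0.7) + 0.8416·√(0.2·0.8 + 0.4·0.6)]² / 0.2² = (1.270 + 0.532)² / 0.04 ≈ 81.2, so 82 per group without continuity correction.

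With correction: n = (n′/4)·[1 + √(1 + 4/(n′·0.2))]² = 20.3·(1 + 1.116)² ≈ 90.9, so 91. The stated figure is reproduced. Planning 110 leaves room for (110 − 91)/110 = 17.3% dropout. No rate by arm is given.

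**2. Which class a filled case takes.**
- Dead: deteriorated, by the separate rule.
- Two or more recorded unscheduled admissions: deteriorated, whatever score is filled.
- Otherwise, filled change of -5 or lower: deteriorated.
- Otherwise, filled change between -5 and +5: unchanged.

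**3. Where the median might lie.** The document gives no spread for the scale. Assume a score SD of 5 to 6 and a baseline to 3-month correlation of 0.6 to 0.7. The SD of change is SD·√(2(1 − r)), from 5·√0.6 = 3.9 to 6·√0.8 = 5.4. Simulating whole-number changes and reading the term as the median among all decliners:
- mean change -0.5: median -3 to -4 (unchanged);
- mean change -2: median -4 in three of the four corners and -5 in one (SD 6, r = 0.6).

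The cut at -5 lies at the edge of this range, so the class cannot be foreseen.

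**4. Effect on the comparison with no true effect.** Let p be the true share improved or unchanged, d the dropout, unrelated to outcome, and f the filled class (0 deteriorated, 1 unchanged). Each arm reports p(1 − d) + f·d. The false difference, intervention minus control, is (f − p)(d_I − d_C).

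With assumed dropout of 10% in control and 25% in intervention, 110 per arm and an uncorrected two-sided 5% chi-square test:

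| p | Filled as deteriorated | Type I error | Filled as unchanged | Type I error |
|---|---|---|---|---|
| 20% | 18% vs 15% (-3 points) | 9% | 28% vs 40% (+12) | 47% |
| 40% | 36% vs 30% (-6) | 16% | 46% vs 55% (+9) | 27% |
| 60% | 54% vs 45% (-9) | 27% | 64% vs 70% (+6) | 16% |
| 80% | 72% vs 60% (-12) | 47% | 82% vs 85% (+3) | 9% |

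Swapping the arms only reverses the sign. With 17% dropout in both arms the difference is 0 and the error about 5% under either fill.

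**5. Which cells fit together.** The filled class and p are linked, because both depend on the distribution of change.
- p = 75% filled as unchanged, which agrees with medians of -3 to -4: dropout of 20% against 10% gives 77.5% vs 80.0% and 7.2%; 25% against 10% gives 77.5% vs 81.25% and 10.4%.
- p = 20%, the planning control rate, filled as deteriorated: 18% vs 16% and 6.8%; 18% vs 15% and 9.3%.
- p = 20% filled as unchanged (47% in the table) is hard to reach. If 80% deteriorate through the score, the median cannot lie above -5; admissions would have to drive most deterioration.
- p = 75% filled as deteriorated gives 21% (20% against 10%) and 40% (25% against 10%). With a mean change of -0.5 it needs a change SD of about 6, above the 3.9 to 5.4 in step 3.
- The one corner in step 3 with a median of -5 has about 32% declining by 5 or more, so p is at most about 68%. At 25% against 10% dropout this lies between the 60% and 80% rows.

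**The case against.** The method is only likely, the article condenses a fuller protocol, and a statistician will be consulted. That stands: the bias of this fill is conditional on its being adopted. What the article does state is that the choice depends on the data and which method is favoured, and both are open to criticism as written.

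The undefined term also has a kinder reading. If the median is taken among participants already classed as deteriorated on the score, it is -5 or lower by definition and agrees with the rationale. This is fair, and it means the contradiction with the rationale is possible rather than certain. It does not remove the single-class problem. A median taken by arm is not excluded either, and would not help, since the two medians could fall on opposite sides of the cut.

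A reader might infer that every dropout lands in one class. The document does not support that: deaths have their own rule, and the admissions criterion already classifies some non-responders from records. A reader might also infer that analysts who know the allocation will pick the rule. The Blinding section says only that participants and intervention staff cannot be blinded, and basing the choice on the data may mean no more than the amount and pattern of missingness.

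Multiple imputation in its standard form assumes that data are missing at random, whereas the article expects non-response to reflect worse health. That is right, and it is why the fix needs a departure-from-random analysis.

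**Conclusion.** The point holds as a weakness that should be fixed before analysis. The favoured fill is undefined, places most missing scores in one class, and lets dropout feed into the primary comparison.

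The size rests on assumed unequal dropout, unrelated to outcome, with no true effect. At 25% against 10% the type I error runs from about 9% to 47% over success shares of 20% to 80%. In the two moderate cases of step 5 it is about 7% to 10% for dropout of 20% to 25% against 10%. Equal dropout with the same filled class gives no inflation.

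The figures of 21% and 40% should not be read as the expected error, because they pair a 75% success share with a fill that moderate assumptions about the scale do not produce. Nor is the 110 per arm a serious defect. With equal 17.3% dropout filled as deteriorated, 20% against 40% becomes 16.5% against 33.1%, and power is 82% uncorrected or 78% corrected, against a target of 80%.

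**What to change.** State the primary missing-data rule before anyone looks at outcome data by arm:

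- Keep death as deteriorated.
- Where recorded admissions alone decide the class, use them even if the questionnaire is missing.
- For other missing self-efficacy scores, impute the score by multiple imputation within arm, using baseline measures and recorded admissions. Add the 6- and 12-month scores only if the timing of the primary analysis allows. Classify after imputation and pool with Rubin's rules.
- Because non-response is expected to reflect worse health, add a delta-adjusted or tipping-point analysis by arm.
- Keep the median-change fill as a sensitivity analysis, stating whose median it is and whether it is taken by arm.

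The cost is some plan wording and modest extra analysis; multiple imputation is already foreseen for the economic evaluation. Confidence intervals will be slightly wider than under a single-value fill, because the uncertainty from missing data is then counted.
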